#### Power and Sample Size Considerations

Considerations of power and sample size in intensive longitudinal studies must include both within- and between-person sources of variation. These sources of variation are influenced differently by the number of measurement points and the number of participants included in the study, complicating calculations (76). This might be one of the reasons why reports of intensive longitudinal studies seldom include power calculations or sample size justifications (82). We conducted general power and sample size calculations for a longitudinal study design (83) targeting outcome variation within participants, in which

$$\begin{array}{l} Power=\frac{n\;x\;m}{1+\left(m-1\right)\;x\;ICC} \end{array}$$

with n indicating number of participants and m indicating measurement points per participant. The intraclass correlation (ICC) states how much variance of a variable is due to temporally stable factors, i.e., between-person variability as opposed to within-person variability (76). This formula can be transformed the following way:

$$\begin{array}{l} n=\frac{Power\;x\;\left(1+m-1\right)\;x\;ICC}{m}\; \end{array}$$

In previous studies, the ICC of the motivational phase variables of interest ranged between 0.54 [for entrapment (24)] and 0.67 [for suicidal ideation (19)], so we chose the upper bound for our calculation. With a desired power level of 80%, 60 expected assessments per person (see above), and an ICC of 0.67, we would need 54 participants overall.

However, given the fact that the estimated compliance rate is not guaranteed and we aim to test several hypotheses, e.g., regarding group differences concerning pre-motivational phase variables, we plan to recruit more participants than the calculated minimum sample size. Therefore, we plan to assess about 50 patients and 100 participants from the general population (as recruitment of the latter is less costly in terms of research staff's time). Empirical investigations of the single hypotheses, including cross-level interactions, will include more specific, simulation-based power analyses making use of resources such as the recently developed app PowerAnalysisIL (84).

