### Selection of Participants

With the combination of a population sample and a patient sample, we aim to achieve variation regarding the variables of interest: On the one hand, rates of suicidal ideation (assessed using EMA) and behavior (assessed retrospectively) in the general population are relatively low (e.g., 9). In a recent survey of a representative German community sample, we found rates below 10% (using the PHQ-9 item) (39) whereas an analysis of the same item based on unpublished routine data of 724 patients treated at the Department of Psychosomatic Medicine and Psychotherapy of the University Medical Center Mainz over the course of 4 years showed rates of 41%. They are considerably higher in clinical populations. On the other hand, individuals in psychiatric and psychosomatic-psychotherapeutic (inpatient) treatment show comparatively greater impairments in personality functioning (40). As we intend to study associations of personality functioning with suicidal ideation and established risk and protective factors (including more complex associations proposed by previous research, such as moderating or mediating effects), it will be beneficial to recruit a substantial number of mentally healthy individuals with higher levels of personality functioning as well.

Inclusion or exclusion criteria, respectively, are the same for the general population and the patient sample. Given that the study focuses on transdiagnostic risk and resilience factors, participation will be open to a broad range of individuals. However, participants need to be able to understand and complete the assessments as intended. This is why individuals with current substance use disorders and psychotic symptoms are not considered eligible. Further exclusion criteria are insufficient knowledge of the German language and the absence of a smartphone for personal use. Lastly, the study focuses on the motivational phase in which suicidal ideation arises. It does not include the study of (risk and protective factors associated with) suicidal behavior/self-harm. As the technical realization of the study neither allows for the personal identification of single participants by the research team nor for the processing of data in a way that would allow for real-time-monitoring and intervention. Therefore, we decided that for safety reasons, acutely suicidal individuals cannot take part.

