#### Expectations Regarding Compliance

Review articles of previous EMA studies found compliance rates of 79% across samples (79) and 77% in studies focusing on self-harm and suicide (26). However, as suicidal ideation, the main construct of interest, has been shown to fluctuate substantially (19, 80), we chose a sampling design with more assessments per day and a longer assessment period than most of the summarized research (e.g., respective mean values were six assessments per day over the course of 1 week (79). Therefore, we expect compliance rates in the present study to be lower, i.e., around 60 of 100 assessments. Studies achieved higher compliance rates when using incentives (79). In this study, we do not communicate a certain target compliance rate to participants (e.g., the completion of >50% of assessments) as we do not want to motivate them to answer prompts without regard to the questions/answering truthfully. However, they are informed that all participants who stay with the study for 10 days are—at the very end—given the opportunity to enter a raffle (of 15€-shopping vouchers for a supermarket). After data collection is completed, individual participants' data might be excluded from the analyses if the free text answer in the end assessment contains information about events that complicate the interpretability of their responses in a substantial way (e.g., technical dysfunction of their mobile phone). Such cases will be made transparent in the study reports. It is also common practice to include only individuals with a certain percentage of completed assessments in the analyses. However, all thresholds (e.g., 15%) applied in this context are somewhat arbitrary. Therefore, we will follow recommendations to only use them in combination with sensitivity analyses using the whole sample, in order to check whether the resulting findings are robust (81). Predictors of signal compliance will also be investigated (e.g., age, gender, symptom burden, and technical/digital competencies).

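### The 54-participant, 80% power statement is not supported for H3.1 and H3.2: it is an effective sample size with no alpha or effect size, and it ignores the protocol's own ideation rates

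*Protocol article*

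**What the plan says.** Under Power and Sample Size Considerations, the protocol article describes a general calculation "targeting outcome variation within participants". Power is set equal to n x m / [1 + (m - 1) x ICC], and this is rearranged to give n. The inputs are:

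- The number of completed prompts: "we expect compliance rates in the present study to be lower, i.e., around 60 of 100 assessments" (Expectations Regarding Compliance).
- The ICC, for which earlier studies gave 0.54 for entrapment "and 0.67 [for suicidal ideation (19)], so we chose the upper bound for our calculation".

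The result is "With a desired power level of 80%, 60 expected assessments per person (see above), and an ICC of 0.67, we would need 54 participants overall". The section treats this as a minimum and goes above it for two reasons, uncertain compliance and the number of hypotheses: "Therefore, we plan to assess about 50 patients and 100 participants from the general population (as recruitment of the latter is less costly". Power for the single hypotheses is left to later simulation.

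Selection of Participants gives ideation rates for both recruitment groups: "In a recent survey of a representative German community sample, we found rates below 10% (using the PHQ-9 item", and, for the same item in 724 patients of one participating department, "over the course of 4 years showed rates of 41" per cent. They serve there to justify combining two samples. They do not appear in the sample size section.

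**The concern.** H3.1 (entrapment is associated with ideation) and H3.2 (loneliness moderates this) carry the primary research goal. The 54-participant statement is the only power figure in the article, and it uses the ICC of ideation, so a reader will take it as covering these hypotheses. Two things stand in the way:

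- The formula cannot yield a power, because nothing in it describes a test.
- It assumes that every participant varies in ideation over time. Someone who answers at the floor at every prompt has no within-person variation in ideation and so contributes nothing to a within-person slope or its moderation. Two thirds of planned enrolment comes from the group with the lower ideation rate.

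If the 80% figure is believed, a null result for H3.2 could be read as evidence against the theoretical model when the study may simply have carried too little information on the interaction.

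**Working it through.** **Inputs.** m = 60 completed assessments, ICC = 0.67, power term 80, planned sample 50 patients + 100 population = 150 ("we plan to assess about 50 patients and 100 participants from the general population"), and PHQ-9 ideation rates of 41% (patients) and below 10% (population).

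**Step 1: reproduce 54.**
- 1 + (m - 1) x ICC = 1 + 59 x 0.67 = 40.53.
- Correct inversion: n = 80 x 40.53 / 60 = 54.04.
- Inversion as printed, with (1 + m - 1) x ICC: n = 80 x 60 x 0.67 / 60 = 53.6.
- Both round to 54, so the misplaced bracket in the printed inversion does not matter here.
- With 0.80 in place of 80, the correct inversion gives 0.80 x 40.53 / 60 = 0.54 participants.

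The figure is therefore reproduced only by entering 80 as a count. The expression n x m / [1 + (m - 1) x ICC] is the design-effect effective sample size, so 54 is the number of people who yield about 80 effective observations (54 x 60 / 40.53 = 79.9).

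**Step 2: do 80 effective observations mean 80% power?** Only for one particular effect. As an illustration, assume a simple correlation test, two-sided 5%, with power approximately Phi(atanh(r) x sqrt(80 - 3) - 1.96):

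| assumed r | power with 80 effective observations |
|---|---|
| 0.1 | 14% |
| 0.2 | 43% |
| 0.31 | 80% |
| 0.4 | 96% |

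The article states no effect size, and this test is not the planned mixed model. The table shows only that the formula leaves power undetermined.

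**Step 3: expected number with any ideation at the protocol's own rates.** Patients: 50 x 0.41 = 20.5. The population rate is given only as an upper bound, so a range is assumed:

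| assumed population rate | expected number of 150 |
|---|---|
| 2% | 20.5 + 2 = 22.5 |
| 5% | 20.5 + 5 = 25.5 |
| 8% | 20.5 + 8 = 28.5 |
| 10% | 20.5 + 10 = 30.5 |

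That is about 22 to 31 people, or 15% to 20% of the sample. At 41% and 10% the central 95% binomial range is 22 to 40.

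**Step 4: how firm is that number?** The Introduction reports that the share of participants showing ideation in earlier intensive longitudinal studies ran from a fifth to all. For 150 people that is 30 to 150. The PHQ-9 figure therefore sits at the low end of the article's own range and is not a ceiling.

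**The case against.** The strongest reply is that the section calls its calculation general, claims no specific reserve for H3, and commits to simulation-based power analyses for each hypothesis. The Discussion also names low ideation and skewed responses as a limitation and offers logistic or any-ideation analyses as a fallback. All of that is true. It does not repair the statement, because 54 participants at 80% power remains in the text as the calculated minimum and nothing commits the later simulations to a proportion of participants at the floor.

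A second reply concerns the count of about 30, and much of it stands:

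- The rates come from one PHQ-9 item. The EMA outcome uses three seven-point items at up to 100 prompts. One of them, the wish to live, may vary in someone who reports no ideation.
- The Discussion says that assessing passive and active ideation together raises detection.
- Against this, the Introduction says detection depended more on the type of sample than on the number of daily prompts, and excluding acutely suicidal people may lower the patient rate.

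Third, H3 is not worded as within-person only. Participants at the floor still inform between-person associations.

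A reader might go further and infer that, since about 30 is below 54, the minimum is not met, or might calculate a specific low power for H3 by treating 54 as the number that gives 80%. The documents support neither. They set 54 as a count of all participants, which 150 exceeds. Because 54 is not a power threshold, neither reaching nor missing it says anything about power for H3. Any percentage built on it needs an effect size that the article does not give.

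**Conclusion.** The concern holds in a limited form. The statement that 54 participants give 80% power is unsupported for H3.1 and H3.2, for two separate reasons. The formula is an effective sample size with no alpha, effect size, slope or interaction. It also treats all participants as varying in ideation, while the protocol's own rates suggest that about 22 to 31 of 150 would report any. The first reason rests on arithmetic alone. The second assumes that the PHQ-9 rates carry over to the EMA items and that the population rate lies between 2% and 10%; the true number could be well above this or somewhat below it.

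The actual power for H3 cannot be worked out from the article. The finding is that 80% has not been shown, not that the study is underpowered by a known amount. The planned 150 may prove adequate once a proper calculation is made.

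**What to change.** In Power and Sample Size Considerations:

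1. Withdraw the 54-participant, 80% statement as a power claim for H3. If the figure is kept, describe it as the number of participants yielding about 80 effective observations.
2. Run the simulation already announced for H3.1 and H3.2 at the planned 50 + 100 mix. State the alpha and effect size, use 60 assessments per person, and vary the proportion reporting any ideation over a range anchored on the article's own figures, for example 20% to 60% overall (30 to 90 of 150 people). Report the resulting power or the minimum detectable slope.
3. Beside each H3 estimate, report how many participants had non-zero within-person variance in ideation.

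This costs some rewording, additional inputs to a simulation that is already planned, and one extra count in the results. No extra participants are needed. The downside is that the stated power for the primary hypotheses may look less favourable.

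### The quantity the protocol calls power is an effective sample size, so 54 participants are not shown to give 80% power for any test

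*Protocol article*

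**What the plan says.** All of this stands in the protocol article under Power and Sample Size Considerations, unless another section is named.

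- The authors report "general power and sample size calculations for a longitudinal study design (83) targeting outcome variation within participants". The formula sets power equal to n × m / (1 + (m − 1) × ICC), "with n indicating number of participants and m indicating measurement points per participant".
- The formula is then rearranged for n. The numerator is printed as power × (1 + m − 1) × ICC and the denominator as m.
- ICCs from previous studies are given as 0.54 for entrapment and 0.67 for suicidal ideation, "so we chose the upper bound for our calculation".
- The value m = 60 comes from Expectations Regarding Compliance: "we expect compliance rates in the present study to be lower, i.e., around 60 of 100 assessments".
- The result is stated as "60 expected assessments per person (see above), and an ICC of 0.67, we would need 54 participants overall", for a target power of 80%.
- About 50 patients and 100 people from the general population are planned, as a margin above this minimum. The reasons given are uncertain compliance and the number of hypotheses, including group differences.
- Work on the single hypotheses "will include more specific, simulation-based power analyses". No inputs, results or timing are given for these.

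**The concern.** Power is the probability that a stated test rejects at a stated alpha when a stated effect is present. The formula contains no test, no alpha and no effect size. It is the standard expression for how many independent observations a clustered data set is worth. Labelling it power and entering 80 turns a target of 80 effective observations into a claim of 80% power.

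At stake is the only power figure in the article. The calculated minimum is the reference point against which 150 is presented as generous. If 54 has no link to power, exceeding it says nothing about power either. The formula also addresses a different kind of quantity from the one the text says it targets. The entrapment effect (Hypothesis 3.1) and its moderation by loneliness (Hypothesis 3.2) are to be tested over repeated assessments in mixed models with random slopes (Data Structure and Analyses).

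**Working it through.** **Inputs.** From the article: m = 60, ICC = 0.67, target 80%, planned n = 150 (50 + 100). Alpha, sidedness, effect size and slope variance are not stated; wherever they appear below they are assumptions.

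**1. Reproducing 54.** Design effect = 1 + (60 − 1) × 0.67 = 40.53. Solving the first printed formula for n gives n = P × 40.53 / 60.
- P = 80: n = 54.04, the published figure.
- P = 0.80: n = 0.54 participants.

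**2. What the formula measures.** The numerator n × m is the total number of observations and the denominator is the design effect.
- n = 54: 54 × 60 / 40.53 = 79.9
- n = 100: 100 × 60 / 40.53 = 148
- n = 150: 150 × 60 / 40.53 = 222

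A quantity that reaches 222 at the planned size is neither a probability nor a percentage. It is a count.

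**3. The rearrangement.** As printed, (1 + m − 1) × ICC = m × ICC, so m cancels and n = 80 × 0.67 = 53.6 whatever the number of prompts. The correct form gives 54.04, and both round to 54. The correct form also barely reacts to m: m = 15 gives 80 × 10.38 / 15 = 55.4, and m = 100 gives 80 × 67.33 / 100 = 53.9.

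**4. What 80 effective observations would give (illustration).** Assumptions: two-sided 5%, a person-level predictor, r as its correlation with the outcome at a single assessment, and the Fisher z approximation. Power ≈ Φ(atanh(r) × √(79.9 − 3) − 1.96).

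| r | Power |
|---|---|
| 0.20 | 43% |
| 0.30 | 77% |
| 0.31 | 80% |
| 0.40 | 96% |

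The 80% label would be true only near r = 0.31, a value the article does not mention.

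**5. Within-person effects.** The design effect describes the precision of a mean or a person-level contrast. A within-person slope depends on other quantities. As a simple approximation without autocorrelation, with the slope in within-person SD units and τ the SD of slopes between people, SE = √((τ² + 1/(m − 1)) / n). For an assumed slope of 0.05:

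| τ | n = 54 | n = 150 |
|---|---|---|
| 0 | 81% | over 99% |
| 0.1 | 61% | 96% |
| 0.3 | 20% | 47% |

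Neither the design effect nor the target of 80 enters this calculation.

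**6. A group contrast such as Hypothesis 1.** The split between people with and without past self-harm is not given. Take an assumed 1:2 split with differences in SDs of a single assessment. The SD of a person mean is √(0.67 + 0.33/60) = 0.82. At n = 150 the SE is 0.82 × √(1/50 + 1/100) = 0.142. Power is 29% for a difference of 0.2 and 94% for 0.5. At n = 54 (18 and 36), power for 0.5 is 56%. The split is for illustration only. It is not the patient versus population split, which is a different contrast from Hypothesis 1.

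**The case against.** The strongest defence is that nothing important depends on 54. It is a floor, and the plan is for 150, about 2.8 times as many (150 / 54). The article calls the calculation general, explains that power in such designs is difficult, and defers the single hypotheses to simulation. It has other reasons for the larger sample: several hypotheses, and uncertain compliance. The second has some force despite the low sensitivity to m, because Expectations Regarding Compliance considers completion thresholds for inclusion, so poor compliance could reduce n as well as m. The arithmetic reproduces, and the bracket may be a typesetting slip, since the first formula is printed correctly.

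All of this stands, and it limits the consequences. It does not make the 80% statement true, and an announced simulation without inputs or results does not replace it.

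A reader might infer more than the article supports:

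- **That the study is underpowered.** Power at 150 runs from low to near 100% depending on inputs the article does not give.
- **That 0.67 is the favourable ICC for within-person effects.** The two ICCs belong to different variables, entrapment as predictor and suicidal ideation as outcome, so one cannot be exchanged for the other. Random slopes add a further component. Within the formula actually used, 0.67 is the cautious choice: 0.54 gives 80 × 32.86 / 60 = 43.8.
- **That the simulations would come after the data.** No timing is stated.
- **That every hypothesis is claimed to have 80% power.** The article does not say so.

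**Conclusion.** The statement is wrong as written. At m = 60 and ICC 0.67, 54 participants correspond to about 80 effective observations for a mean or person-level comparison, and the article contains no valid power figure. This follows from the printed formulas and inputs alone. The illustrations in steps 4 to 6 rest on assumed alpha, effects, slope variance and split; they show only how far power depends on what is not stated.

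Two lesser errors belong to the same section. The rearranged formula loses its dependence on m, with no effect after rounding. The design effect also does not address the within-person variation that the text says is its target.

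The error lies in what the quantity means, not in the arithmetic. The planned sample of about 150 is neither supported nor contradicted by it.

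**What to change.** 1. Withdraw the statement that 54 participants give 80% power. Say instead that 54 participants with 60 assessments at ICC 0.67 correspond to about 80 effective observations for a mean or person-level comparison.
2. Relabel the left-hand side of the first formula as effective sample size, N_eff. Correct the rearrangement to n = N_eff × (1 + (m − 1) × ICC) / m.
3. Remove the claim that this calculation targets within-person variation, and stop presenting 54 as a power-based minimum that supports 150.
4. Use the simulation already announced to report what about 150 participants and about 60 assessments deliver. Cover Hypothesis 1 (past self-harm yes or no, over a range of assumed splits) and Hypotheses 3.1 and 3.2. State alpha, effect sizes, ICCs and random-slope variance as assumptions.

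The cost is one rewritten paragraph and a short simulation. Recruitment does not change. The article loses a reassuring figure and gains one that can be checked.

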## Discussion of Strengths and Limitations

In summary, the main objectives of the TempRes study concern the validation of a part of the established, influential IMV model and the integration of powerful, empirical methods allowing for the modeling and differentiation of between- and within-person effects with recent developments in the operationalization of the level of personality functioning. Building on current research advances, the project aims to contribute to a better understanding of suicidal ideation in both at-risk groups and the community to inform prevention and intervention efforts. A recent systematic review (27) showed that assessing both passive and active suicidal ideation—as this study will do—increased detection rates of suicidal ideation. Further, the EMA module includes both theoretically-based, specific constructs [such as entrapment, e.g., (85)] and broader categories of subjective experience [such as negative affect, e.g., (20)] that were associated with suicidal ideation in previous research. The present study is also implemented in such a way that both participant data privacy and open science principles, such as the provision of anonymized study data, have a high priority.

However, there are several limitations. As mentioned, low proportions of individuals reporting suicidal ideation, especially in non-clinical populations, present a challenge to empirical research on associated risk and protective factors. The present study tries to address it by combining different samples. However, if responses on the respective items yield a highly skewed distribution, it might be necessary to adapt the analysis strategy (either by calculating logistic mixed-effects models or by summarizing instances of any level of suicidal ideation). Further, anonymity in responses and the absence of incentives/guaranteed reimbursement might hamper compliance and implicate comparatively low participation rates. As the EMA module only assesses suicidal ideation, the study cannot give insight into time-varying risk and protective factors underlying suicidal behavior. The exclusion of acutely suicidal individuals (which we deemed necessary for safety reasons) represents a further limitation as it means that the resulting findings might not apply to those individuals with the highest risk. In future research with the appropriate resources, they should be included, and their responses should be closely monitored (41). Indications of acute risk should also receive some sort of reaction. However, as it is unclear whether pop-up notifications are read and perceived as helpful in case of acute risk (47), ideally, trained staff should be available to reach out to participants, e.g., by phone.

Lastly, it will not be feasible to recruit a representative sample of the population or of the patients treated at the participating departments. There might be specific self-selection effects (including motivational aspects and expectations of the study) which we can neither assess nor statistically control for. However, we intend to compare study participants' characteristics (e.g., gender distribution, age, level of education, symptom burden) with both routine data collected on all consecutive patients treated at the clinics during the trial period and representative survey data of the general population.

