#### EMA Module

In Sample Research, notifications are planned for all 100 scheduled assessment of the EMA module and for the end assessment. The former are sent via push messages at preset times (pseudo-randomized intervals between 8 a.m. and 10 p.m., with a minimum interval of 45 min) to each participant. Each push message contains the same link to the EMA survey on SoSci Survey. Respondents need only click on the link and answer the questionnaire in their browser.

Each assessment includes fewer than 25 items in total. All items except the context variables will use the same response format (1 = “not at all” to 7 = “very”). Context items will assess where participants are currently (e.g., at home, at work) and whether they are alone or have company. Suicidal ideation will be measured using three items adapted from the Beck Scale for Suicide Ideation (51) (“I have a wish to die,” “I have a wish to live,” “I have a wish to kill myself”). As suicidal ideation is not a uniform construct (see Introduction), this kind of assessment allows for the differentiation of a wish to die (i.e., passive death wishes), wish to live, and wish to end one's life (i.e., active suicidal ideation). It will be placed in the middle of the administered items to reduce participants' reactivity to it. The same applies to defeat, entrapment [assessed with two items each, drawn from the German Defeat Scale (DS-d) (68) and the German Entrapment Scale (ES) (69)] and loneliness [assessed with two items, adapted from Kleiman, Turner (19)]. Additional items include positive and negative affect, which will be measured using items drawn from the German PANAS-X (70, 71). Lastly, two items drawn from the Beck Hopelessness Scale (52) will assess hope/hopelessness.

Items were chosen based on their psychometric properties (e.g., those with the highest factor loadings of their respective scales in the questionnaire long form). In cases where items were drawn from longer scales, we checked whether their wording needed to be adapted to the “here and now.” However, this was not necessary as the original questionnaires communicated the time period of interest as part of the instruction rather than as part of the items themselves. The sequencing of items does not change throughout the study.

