### Data Structure and Analyses

Analyses will be conducted using R (72) and mainly using the packages esmpack (73), lme4 (74), and lmerTest (75).

The special survey methodology implicates a longitudinal and nested data structure in which the measurement points (Level 1) are nested within days (Level 2) which are in turn nested in participants (Level 3). This is why the main analyses will build on linear mixed models, a technique in which separate regression functions are estimated for each cluster. Such models expand the standard regression model by random effects that allow for the investigation of person-level differences in model coefficients [see e.g., (76, 77)]. Models will include random intercepts and random slopes (i.e., the deviations of participants' values from the respective group mean) and account for autocorrelation. Moderation effects will be probed by creating the product of the mean-centered variables of interest (entrapment and loneliness). In the case of statistically significant interaction effects, the steepness of the regression line on different values of the moderator (i.e., entrapment) will be visualized (e.g., for the sample mean and the sample mean +/– one standard deviation).

The primary outcome is suicidal ideation. Its operationalization via three items allows for tests of construct validity and reliability [e.g., as nested α (78)]. Secondary outcomes are entrapment and loneliness.

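### The fallback named for skewed ideation ratings discards changes in severity above the floor; a prompt-level ordinal mixed model would keep them, for a modest gain in power

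*Protocol article*

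**What the plan says.** Under EMA Module, momentary ideation is measured with three items, and "All items except the context variables will use the same response format", a scale from 1 to 7. Under Data Structure and Analyses, ideation is the primary outcome ("The primary outcome is suicidal ideation. Its operationalization via three items allows for tests of construct validity and reliability") and "the main analyses will build on linear mixed models", with random intercepts, random slopes and an allowance for autocorrelation. The R packages listed as mainly used include lme4 and lmerTest; no package specific to ordinal mixed models is named.

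The Discussion of Strengths and Limitations adds that, if the item responses turn out highly skewed, the strategy might have to change, "either by calculating logistic mixed-effects models or by summarizing instances of any level of suicidal ideation". No third option is named.

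Selection of Participants gives ideation rates on the PHQ-9 item of below 10% in a community sample and 41% in patients. Power and Sample Size Considerations plans about 100 population participants and 50 patients, expects 60 answered prompts each, and adopts an intraclass correlation (ICC) of "0.67 [for suicidal ideation (19)], so we chose the upper bound for our calculation".

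**The concern.** The study sends up to 100 prompts per person because ideation fluctuates, and Hypotheses 3.1 and 3.2 ask whether it moves with entrapment, and more so when the person is lonely. An any/none cut records only crossings of the floor. Someone who moves between 2 and 6 all week is constant at yes and adds almost nothing to a within-person slope. With an ICC as high as 0.67, people with ideation tend to stay above the floor, so the loss falls on those who carry most of the signal. The question also narrows from how strong ideation is to whether there is any.

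The second option is less clear. If it means a count per person or per day, ideation is no longer paired with entrapment and loneliness at the same prompt, and the momentary association and its moderation cannot be tested from it.

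Skew does not force either choice. A cumulative-link mixed model treats the floor as one category and uses all seven levels.

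**Working it through.** **The plan's own figure.** The sample size of 54 reproduces: 80 × (1 + 59 × 0.67) / 60 = 54.04, or 53.6 from the formula as printed, with power entered as the number 80. It uses no effect size and no outcome coding, so it says nothing about the fallback.

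**Inputs from the article.** 100 population and 50 patient participants; 60 answered prompts; ICC 0.67, with 0.54 (the article's value for entrapment) as a lower check; rates of 10% (upper bound) and 41%. These rates average (100 × 0.10 + 50 × 0.41) / 150 = 20% over the planned mix. They are rates of persons; the article gives no share of prompts at the floor.

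**Assumptions.** Latent normal ideation, between-person variance = ICC, within-person variance = 1 − ICC, six equally spaced cut-points 0.25 to 1.0 latent SD apart, two-sided alpha 0.05. There are two readings of the rates:
- Person-level: 10% and 41% of persons have ideation at 5% or more of prompts. About 94% (ICC 0.67) or 95% (ICC 0.54) of ratings are then at the floor.
- Prompt-level: 10% and 41% of prompts are above the floor. About 80% of ratings are then at the floor.

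**Formulae.** The information per prompt for a within-person shift is i = Σ[φ(z_{k−1}) − φ(z_k)]² / p_k. It is computed for seven categories and for the floor cut alone, then averaged over the distribution of person means. R is the ratio of the two. Power with the ordinal model, where the any/none cut has 80%, is Φ((1.96 + 0.842)√R − 1.96). With a random slope of SD τ (in within-person SDs), each person's information 60i becomes 60i / (1 + 60i·τ²) before averaging.

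**Random intercepts only.**

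| Reading | ICC | R | Information lost by the cut (1 − 1/R) | 80% becomes |
|---|---|---|---|---|
| Person-level | 0.67 | 1.09-1.17 | 8-14% | 83-86% |
| Person-level | 0.54 | 1.06-1.10 | 5-9% | 82-84% |
| Prompt-level | 0.67 | 1.24-1.35 | 19-26% | 88-90% |
| Prompt-level | 0.54 | 1.19-1.26 | 16-21% | 86-88% |

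Two examples: R = 1.09 gives 2.802 × 1.044 − 1.96 = 0.965, or 83%. R = 1.35 gives 2.802 × 1.162 − 1.96 = 1.296, or 90%.

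**With random slopes, as the article plans (ICC 0.67).** On the person-level reading, 80% becomes 82-84% at τ = 0.1 and 81-82% at τ = 0.2. On the prompt-level reading it becomes 86-88% and 84-85%.

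**Cross-check with a logistic latent model.** Here the information is p(1 − p) for the cut and (1 − Σp_k³)/3 for seven categories, with random intercepts. At ICC 0.67 the efficiency of any/none against ordinal is 0.75, 0.86 and 0.91 with 75%, 90% and 95% of ratings at the floor. An ordinal power of 80% then corresponds to about 68%, 74% and 76% with the cut. At ICC 0.54 the efficiencies are 0.82, 0.92 and 0.95. The loss therefore shrinks as skew grows. Ignoring clustering, it would be only 0.1-8% (59% to 95% at the floor), so the cost is specific to within-person effects.

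**Simulations, random intercepts only.** With 80% at the floor, 60 simulated trials gave mean standard errors of 0.0315 (ordinal) and 0.0355 (any/none), a relative efficiency of 0.79, or about 70% power instead of 80%. The raw rejection rates in those 60 trials (80% and 78%) are too noisy to use. On the prompt-level reading, 200 data sets for the Hypothesis 3.2 interaction gave power of 0.785 (ordinal) and 0.67 (any/none).

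**Merging.** At spacing 0.25 on the prompt-level reading (ICC 0.67), merging to four levels lowers R from 1.35 to 1.22.

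**The case against.** The strongest reply is that the sentence commits to nothing. It sits among the limitations, it is conditional twice over, and the linear mixed model remains the planned analysis. Logistic is not defined as any/none; a cumulative logit model is also logistic, and the software list says only which packages are mainly used. Summarising instances could mean pooling passive and active ideation at a single prompt, which keeps the momentary pairing. The article also promises simulation-based power analyses for each hypothesis.

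Most of this stands, and it limits the point. A reader might infer that the fallback costs ten or more points of power. That needs the PHQ-9 rates, which count persons, to be read as shares of prompts, and it leaves out the random slopes that the article plans. The simulated contrast of 0.785 against 0.67 rests on both, and on data generated under the same shift model that the ordinal analysis assumes. A reader might also infer that Hypothesis 3.2 becomes untestable. That follows only if instances are counted per person or per day, which the text does not say; this option was not quantified.

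The objection does not remove the core. Binary is the usual meaning of a logistic mixed model and is what lme4 fits. The article names only two adaptations and gives no reason for giving up the graded scale. The promised power analyses would not restore severity information that a later recoding removes.

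**Conclusion.** The point holds as a cheap improvement of modest size. On the ordinary readings, both named adaptations discard severity above the floor, and a method that keeps it is available. The most defensible gain, from 80% power with the cut, is about 1 to 6 percentage points: 82-86% with random intercepts only and 81-84% with modest random slopes, both taking the rates as person-level. The 86-90% range is an upper case that needs prompt-level rates and no slope variation.

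All figures assume a latent normal outcome with the quoted ICC on that scale, proportional shifts and equal cut-point spacing. The slope SDs of 0.1-0.2 are also assumed. The gain is smallest under extreme skew, which is where the fallback is most likely to be used.

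**What to change.** In the Discussion of Strengths and Limitations, replace the two options with a statement along these lines: under high skew, the prompt-level 1-7 ratings are analysed per item, or as ordered levels of a score, with a cumulative-link mixed model that has the same fixed and random effects as the linear model, merging sparse upper categories if needed. Keep the any/none logistic mixed model as a sensitivity analysis, and use summaries of instances for description only. If an ordinal model was meant all along, saying so settles the first option.

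The cost is a change of wording and one more standard R package, with no new data. The downsides are small. Proportional odds needs a check, for which the any/none model is a useful comparison. Fitting is slower and may need a simpler random-effects structure. Merging categories gives back part of the gain.
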